### Blinding, unblinding and treatment discontinuation

#### Blinding

All participants and investigators will be blinded to the treatment allocation. OUCRU clinical trials unit (CTU) pharmacists will create blinded drug packages (in fully made-up and labelled treatment packs) containing either active drugs or identical placebo sufficient for 6–8 weeks of treatment (dependent on the MRC grade of the participant) according to the prespecified randomisation list, and pre-ship them to the sites. After randomisation, the ward or trial research nurse will take the completed prescription form to the site pharmacy; they will dispense the trial-number specific pack containing the study drug. Unused drug will be returned to the site pharmacy if a participant withdraws from treatment. In ancillary study 3 MRI brain images will be read by an independent neuroradiologist, blinded to the treatment allocation and outcomes of the participant.

#### Unblinding

If, in the opinion of the local clinician, it is important for good clinical care to unblind treatment the documented request will be discussed with the site Principal Investigator (PI) and Chief Investigator (CI). If it is agreed that knowledge of treatment allocation is essential for the best management of the patient, the unblinding code will be provided by the study pharmacist holding the randomisation list at OUCRU CTU upon documented request from the CI. Generalised clinical deterioration is not sufficient for unblinding, given equipoise about the evidence base supporting the use of dexamethasone regardless of clinical severity. All instances of unblinding will be recorded and reported to the Data Monitoring Committee (DMC) and Trial Steering Committee (TSC).

#### Protocol treatment discontinuation

An individual participant may stop study drug early for any of the following reasons: Participant no longer believed to have TBM and all anti-tuberculosis treatment stopped; Unacceptable toxicity or adverse event; Intercurrent illness that prevents further treatment; Any change in the participant’s condition that justifies the discontinuation of treatment in the treating physicians opinion and after discussion with the site PI; Inadequate compliance with the protocol treatment in the judgement of the treating physician; Withdrawal of consent for treatment by the participant.

### Trial management

#### Interventions

All participants will receive the standard of care anti-tuberculosis drugs according to national guidelines. Each participant will be LTA4H genotyped. The enrolment and randomisation of the participant into the trial will be finalised according to genotype. TT-genotype participants will be treated with anti-tuberculosis drugs and open label dexamethasone (
Table 2). LTA4H CC- and CT-genotype participants will be randomised to receive dexamethasone or placebo for 6–8 weeks, in addition to anti-tuberculosis drugs, dependent upon disease severity (
Table 2). Study drug will be dispensed at randomisation from the site pharmacy in intravenous and oral (tablet) formulations. Placebo will be identical in appearance to active drug and dosed and dispensed in the same way.

**Table 2. T2:** Study drug treatment regimen following randomisation.

	MRC Grade I Daily dexamethasone dose/route	MRC Grades II and III Daily dexamethasone dose/route
Week 1	0.3 mg/kg/24 hrs IV	0.4 mg/kg/24 hrs IV
Week 2	0.2 mg/kg/24 hrs IV	0.3 mg/kg/24 hrs IV
Week 3	0.1 mg/kg/24 hrs IV	0.2 mg/kg/24 hrs IV
Week 4	3mg/24 hrs oral	0.1 mg/kg/24 hrs IV
Week 5	2mg/24 hrs oral	4 mg/24 hrs oral
Week 6	1 mg/24 hrs oral	3 mg/24 hrs oral
Week 7	Stop	2 mg/24 hrs oral
Week 8		1 mg/24 hrs oral

Participants for the DILI strategy study will be randomised to one of three strategies (
Figure 2): Strategies are as follows:

1)Observe: measure transaminases, bilirubin, and INR every 3 days; do not change/stop anti-tuberculosis drugs unless transaminases rise to ≥10x normal, or total bilirubin rises >2.5mg/dl (>43 µmol/L), or INR >1.5 or symptoms of hepatitis worsen (nausea, vomiting, abdominal pain), in which case go to Strategy 3.2)Stop pyrazinamide alone. Observe, measuring transaminases, bilirubin, and INR every 3 days. If transaminases do not fall to <5x ULN by day 5, or total bilirubin rises >2.5mg/dl (>43 µmol/L), or INR >1.5 or symptoms of hepatitis worsen at any time (nausea, vomiting, abdominal pain), go to Strategy 3.3)Current standard of care (current US CDC guidelines
^9^,
Supplementary File 2).

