### Complications of TBM

Hydrocephalus, stroke, and tuberculoma formation are important and common complications of TBM
^3^, however little evidence exists to guide their optimal management. Drug induced hepatitis associated with anti-tuberculosis treatment occurs in around 10% of HIV-uninfected patients
^4^, and can be attributed to rifampicin, isoniazid or pyrazinamide. Determining which drug is responsible is difficult. Corticosteroid therapy leads to hyperglycaemia, and during treatment of TBM dexamethasone may worsen, or reveal, diabetes. Severe hyponatraemia (low plasma sodium), high temperature and CO
_2_ retention all exacerbate raised intracranial pressure and require active management. The role of corticosteroids in adrenal suppression in TBM requires further investigation.

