## Inclusion and exclusion criteria

### Inclusion criteria

Study participants for LAST ACT must be adults (aged 18 years or older), HIV-uninfected, with a clinical diagnosis of TBM (≥5 days of meningitis symptoms, and CSF abnormalities) and anti-tuberculosis chemotherapy either planned or started by the attending physician. Participants will be considered eligible for enrolment in this trial if they fulfil all the inclusion criteria and none of the exclusion criteria. The inclusion and exclusion criteria apply at the point of consent, just before the patient’s blood is sent for LTA4H genotyping. Therefore, it is possible that when the LTA4H genotype result returns and the patient is randomised, the patient will have had >3 days of corticosteroids and/or >6 days of anti-tuberculosis treatment. This is acceptable, although the total duration of corticosteroid and anti-tuberculosis treatment before randomisation must be recorded. The time for an LTA4H result to return is not anticipated to be >3 days (e.g. taken on a Friday afternoon and processed on a Monday morning). As TBM is a serious infection requiring hospitalisation, all eligible participants will be treated in hospital, at least for the initial 3 weeks of their illness.

Study participants for the DILI strategy study must be receiving first-line anti-tuberculosis drugs and fulfil the definition of drug-related liver injury: elevation of blood transaminase concentrations ≥3 times the ULN with symptoms and signs of hepatitis (vomiting, abdominal pain, jaundice), or ≥5 times the ULN or a rise in serum bilirubin >2.0mg/dL (>34 µmol/L) without symptoms
^9^, and less than 90 days of anti-tuberculosis drugs given.

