#### Anti-tuberculosis treatment

First line anti-tuberculosis treatment will follow current Vietnamese national guidelines. Rifampicin (10mg/kg/24 hrs; maximum 600mg), isoniazid (5mg/kg/24hrs; maximum 300mg), pyrazinamide (25mg/kg/24hrs; maximum 2g) and ethambutol (20mg/kg/24 hrs; maximum 1.2g) will be given for at least the first 2 months of treatment, provided drug resistance is not suspected or proven. Pyrazinamide will then be stopped and rifampicin, isoniazid and ethambutol (at the same doses) will then be given until at least 12 months anti-tuberculosis treatment in total has been given. The best treatment of TBM caused by isoniazid-resistant tuberculosis is uncertain, and the attending physician should decide which option to take. For participants with MDR tuberculosis, second-line treatment should be given as soon as possible, following national guidelines and local policies.

Participants with abnormal liver function tests (LFTs) at screening are eligible to enter the trial. These patients should be given standard first-line anti-tuberculosis treatment unless blood transaminase concentrations are ≥3 times the ULN with symptoms and signs of hepatitis (vomiting, abdominal pain, jaundice), or ≥5 times the ULN or a rise in serum bilirubin >2.0mg/dL (>34 µmol/L) without symptoms. In these participants, initial anti-tuberculosis treatment should consist of levofloxacin, ethambutol, and an aminoglycoside (either kanamycin, amikacin or streptomycin). LFTs should be monitored every 3 days and rifampicin started as soon as blood transaminases are <5x the ULN and/or the symptoms and signs of hepatitis resolve. Once the participant is tolerating a rifampicin-containing regimen isoniazid can be introduced and, if isoniazid is tolerated, the aminoglycoside can be stopped. If pyrazinamide is not used in treatment, at least 12 months of anti-tuberculosis treatment must be given. Participants with liver dysfunction at the start of treatment that require modified initial anti-tuberculosis treatment regimens are ineligible for the DILI strategy study.

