### Clinical assessment

Clinical assessment will include conscious level by GCS, new or ongoing focal neurological deficit, clinical treatment response, all serious adverse events, all adverse events of any grade leading to modification of anti-tuberculosis treatment or its interruption/early discontinuation (and clinician-assessed likelihood of relationship of adverse event to dexamethasone), and adherence to drugs (study drug and anti-tuberculosis drugs). Assessment of disability by the modified Rankin scale will be performed at day 30 from randomisation, monthly until completion of anti-TB drugs, and at month 12.

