### Liver function

Alanine transaminase (ALT) and bilirubin will be measured to evaluate liver toxicity every 7 days until discharge and at each subsequent follow-up visit until anti-tuberculosis treatment stops.

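### After its day-5 check, DILI Strategy 2 has no mandatory switch for an isolated transaminase rise to ≥10x ULN, although the same value switches a Strategy 1 participant

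*Protocol article*

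**What the plan says.** The protocol article describes the three DILI strategies under Interventions.

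- **Strategy 1 (observe).** The instruction is "do not change/stop anti-tuberculosis drugs unless transaminases rise to ≥10x normal", or bilirubin exceeds 2.5 mg/dl, or INR exceeds 1.5, or symptoms worsen. Any of these sends the participant to Strategy 3. None has a time limit.
- **Strategy 2 (stop pyrazinamide only).** Transaminases, bilirubin and INR are measured every 3 days. The participant goes to Strategy 3 under the condition "If transaminases do not fall to <5x ULN by day 5", or on the same bilirubin and INR limits, or if "symptoms of hepatitis worsen at any time".

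Entry to the DILI study (Inclusion criteria) is possible with "elevation of blood transaminase concentrations ≥3 times the ULN with symptoms and signs of hepatitis", with ≥5x ULN without symptoms, or on a bilirubin rise alone. Some participants can therefore enter with transaminases below 5x ULN. The primary endpoint covers the 60 days after DILI randomisation and is the proportion of that time in which neither rifampicin nor isoniazid is given or the participant is dead. The comparison of strategies is open.

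**The concern.** Both experimental strategies deliberately continue rifampicin and isoniazid during liver injury, so the rules that end continuation are the main individual safeguard. Strategy 1 names a transaminase level at which continuation ends. Strategy 2 names one only for the day-5 check.

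Stopping pyrazinamide does not make a later rise impossible. Complications of TBM says that hepatitis on this treatment "can be attributed to rifampicin, isoniazid or pyrazinamide", and that it is hard to tell which drug is responsible. Strategy 2 continues two of the three candidates.

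Two things are at stake. One is the safety of a participant with a late rebound. The other is consistency of conduct: the same laboratory value leads to a switch by rule in one experimental arm and by unblinded judgement in the other, in a study whose endpoint is time off the two drugs.

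**Working it through.** The plan has no figure of its own to reproduce here. The check sets the two switch rules side by side and applies them literally.

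**Triggers**

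| Trigger | Strategy 1 | Strategy 2 |
|---|---|---|
| Transaminases | ≥10x, no time limit | not <5x ULN by day 5 only |
| Bilirubin >2.5 mg/dl | yes | yes |
| INR >1.5 | yes | yes |
| Worse symptoms | yes | yes |

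The phrase about any time in Strategy 2 follows the symptom trigger. It cannot extend a transaminase condition that already carries its own date.

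**Illustrative courses.** The transaminase values below are assumed. Bilirubin and INR are normal and symptoms are not worse. Tests fall every 3 days from DILI randomisation, so the day-5 check is read from the day-6 test. Strategy 1's reference to normal is read as ULN.

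| Course (multiples of ULN) | Strategy 1 switches | Strategy 2 switches |
|---|---|---|
| 7, 6, 4, 4, then 12 on day 12 | day 12 | never |
| Entry at 3.5 with symptoms, 4 on day 6, 12 on day 9 | day 9 | never |
| 7, 6, 4, 4, then 6 on day 12 | never | never |
| 7 throughout | never | at the day-5 check |
| 7, then 11 on days 3 and 6 | day 3 | at the day-5 check |
| 7, 11 on day 3, 4.5 on day 6 | day 3 | never |

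Rows 1 and 2 show the gap: a late rise to ≥10x after passing the check, or after entering below 5x and staying there until the check. In row 3, a late rise that stays below 10x, the arms agree. In row 4 Strategy 2 is the stricter arm. Rows 5 and 6 show that before day 5 Strategy 2 has no transaminase trigger either.

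**Extent in time.** With day 5 counted from DILI randomisation, 60 − 5 = 55 days of the endpoint window have no Strategy 2 transaminase trigger; 55/60 = 91.7%.

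**Extent in people.** Recruitment and retention anticipates 170 participants, randomised 1:1:1: 170/3 = 56.7, about 57 in Strategy 2. LAST ACT contributes around 70: 70/3 = 23.3, about 23.

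**Search for a rule elsewhere.** Protocol treatment discontinuation concerns the study drug, not the anti-tuberculosis drugs. Liver function sets a testing schedule without an action level. Interim analyses provides for Data Monitoring Committee review of hepatic failure by arm, which is aggregate oversight. The thresholds in Anti-tuberculosis treatment apply to liver dysfunction at the start of treatment. None supplies a later transaminase rule for Strategy 2.

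**The case against.** The strongest reply is that the two rules differ in kind. Strategy 1 bars clinicians from changing the drugs and so must say when the bar lifts. Strategy 2 contains no such bar. A clinician who sees ≥10x may act, and Clinical assessment expects to record "all adverse events of any grade leading to modification of anti-tuberculosis treatment or its interruption/early discontinuation". Bilirubin, INR and symptom triggers stay in force, and tests are done every 3 days. All of this stands. A reader might infer that Strategy 2 participants must stay on rifampicin and isoniazid whatever their transaminases. The text does not say so; what is missing is a mandatory switch.

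A second reply is that the instruction to observe in Strategy 2 carries over the Strategy 1 rules. This is weak. Strategy 2 restates the bilirubin, INR and symptom triggers in full, and the ≥10x limit is the one it leaves out.

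A third reply concerns the first five days. The wait until day 5 can be read as giving pyrazinamide withdrawal time to work, so the lack of an earlier trigger is not clearly an error.

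It is also tempting to set the gap against Anti-tuberculosis treatment, which has "rifampicin started as soon as blood transaminases are <5x the ULN" and/or once hepatitis resolves. Those patients had liver dysfunction at the outset and are ineligible for the DILI study, whose purpose is to test continuing the drugs. That comparison does not establish that ≥10x is unsafe here.

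Finally, Figure 2, Supplementary File 2 and the full protocol are not available, and one of them may carry a further limit. In that case the article text would need only to be aligned with it.

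**Conclusion.** The point holds as a minor gap in an ancillary study. Read literally, Strategy 2 has no mandatory switch for an isolated rise to ≥10x ULN in the 55 days after its day-5 check, although the protocol uses that level to end continuation in Strategy 1. Strategy 2 is not laxer throughout, since it switches participants who stay between 5x and 10x at day 5 and Strategy 1 does not.

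At most the Strategy 2 arm of about 57 people is affected, and within it only those with a late isolated rise. The documents give no frequency for this. A reader might infer a calculable bias in the DILI endpoint, but the documents do not support one. The 16-day median interruption in the sample size section comes from patients with clinical hepatitis or jaundice, not isolated enzyme rises, and the Wilcoxon rank sum test does not test a shift in the arm mean.

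The conclusion assumes that normal and ULN mean the same reference, that day 5 is counted from DILI randomisation, and that no document not shown supplies the limit.

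**What to change.** Keep the day-5 check as it is. Add to the Strategy 2 triggers: or, after the day-5 check, transaminases rise to ≥10x ULN. Write ULN in Strategy 1 as well, and align Figure 2 if it has the same wording.

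If the sponsor also wants early cover, the trigger can include a rise to ≥10x ULN before day 5, accepting that some participants would leave Strategy 2 before pyrazinamide withdrawal has been tested. It should then be worded as a rise, because the entry criteria set no upper transaminase limit and a participant may be randomised already at that level. If no later ceiling is intended, the protocol should say so and give the reason.

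The cost is a one-line amendment. No extra samples are needed: Strategy 2 already tests every 3 days, and under Liver function "Alanine transaminase (ALT) and bilirubin will be measured to evaluate liver toxicity every 7 days until discharge", then at each follow-up visit until anti-tuberculosis treatment stops. The downside is some additional switches to Strategy 3. They are likely to be few in an arm of this size, but the documents do not allow a number.

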#### Anti-tuberculosis treatment

First line anti-tuberculosis treatment will follow current Vietnamese national guidelines. Rifampicin (10mg/kg/24 hrs; maximum 600mg), isoniazid (5mg/kg/24hrs; maximum 300mg), pyrazinamide (25mg/kg/24hrs; maximum 2g) and ethambutol (20mg/kg/24 hrs; maximum 1.2g) will be given for at least the first 2 months of treatment, provided drug resistance is not suspected or proven. Pyrazinamide will then be stopped and rifampicin, isoniazid and ethambutol (at the same doses) will then be given until at least 12 months anti-tuberculosis treatment in total has been given. The best treatment of TBM caused by isoniazid-resistant tuberculosis is uncertain, and the attending physician should decide which option to take. For participants with MDR tuberculosis, second-line treatment should be given as soon as possible, following national guidelines and local policies.

Participants with abnormal liver function tests (LFTs) at screening are eligible to enter the trial. These patients should be given standard first-line anti-tuberculosis treatment unless blood transaminase concentrations are ≥3 times the ULN with symptoms and signs of hepatitis (vomiting, abdominal pain, jaundice), or ≥5 times the ULN or a rise in serum bilirubin >2.0mg/dL (>34 µmol/L) without symptoms. In these participants, initial anti-tuberculosis treatment should consist of levofloxacin, ethambutol, and an aminoglycoside (either kanamycin, amikacin or streptomycin). LFTs should be monitored every 3 days and rifampicin started as soon as blood transaminases are <5x the ULN and/or the symptoms and signs of hepatitis resolve. Once the participant is tolerating a rifampicin-containing regimen isoniazid can be introduced and, if isoniazid is tolerated, the aminoglycoside can be stopped. If pyrazinamide is not used in treatment, at least 12 months of anti-tuberculosis treatment must be given. Participants with liver dysfunction at the start of treatment that require modified initial anti-tuberculosis treatment regimens are ineligible for the DILI strategy study.

#### Management of hepatitis B

Treating participants infected with hepatitis B (HBsAg positive) with corticosteroids carries a very small risk of reactivation and flare of hepatitis B infection
^10,
11^. In order to ensure the safety of patients we will:

1)Test all enrolled participants for HBsAg at baseline (day 0).2)After randomisation (of CT or CC- genotypes) to dexamethasone or placebo, all HBsAg positive participants will be unblinded with respect to the study drug.3)HBsAg positive participants randomised to dexamethasone (CT- or CC- genotypes) will receive tenofovir therapy at 300mg once daily. Tenofovir therapy will be for the duration of dexamethasone therapy, and then for a further 12 months after completion of dexamethasone therapy.4)HBsAg positive participants (of any LTA4H genotype) randomised to placebo will NOT receive tenofovir therapy. Unblinding of HBsAg positive participants is necessary to identify those requiring tenofovir.5)HbSAg positive TT- genotype participants, all of whom will receive open label dexamethasone, will also receive tenofovir therapy at 300mg once daily, according to the current standard of care for HBsAg positive patients as issued by the Vietnam Ministry of Health. Tenofovir therapy will be for the duration of dexamethasone therapy, and then for a further 12 months after completion of dexamethasone therapy.6)LFTs and hepatitis B viral load testing will be performed in those participants with hepatitis B who are receiving dexamethasone. LFTs will be performed at least weekly until discharge, and then every 3 months for the full duration of the study. Liver function tests will be performed more frequently if there is a clinical need. Hepatitis B viral load testing will be performed every 3–6 months (following national guidelines) for the full duration of the study. Participants who are HBsAg negative, but HBcAb positive (i.e. evidence of past hepatitis B infection) will not receive tenofovir and will therefore not be unblinded, but they will be followed carefully for evidence of episodes of hepatitis. The monitoring of HBcAb positive participants (LFTs and hepatitis B viral load testing) will be as for HBsAg patients.

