### Secondary endpoints – main trial

The secondary endpoints of the main trial are as follows:

a)Overall survival during a follow-up period of 12 months. Overall survival is defined as the time from randomisation to death, during a follow-up period of 12 months. Survivors known to be alive at 12 months will be censored at that time-point and subjects who withdrew or were lost to follow-up before 12 months will be censored at the date they were last known to be alive.b)Neurological disability at 12 months. Disability will be assessed by the modified Rankin scale (
Table 1) on days 30 and 60 from randomisation, and then monthly until the end of anti-tuberculosis drugs. The main endpoint is the 12-month assessment and subjects who died before 12 months will be treated as having a score of 6 (‘Dead’).c)Severe (grade 3&4) and serious adverse events. Comparison of the frequency of severe and serious adverse events between treatment groups will form an important part of the study analysis.d)Requirement for ‘rescue’ corticosteroids. Neurological complications occurring after the start of anti-tuberculosis chemotherapy for TBM are common. The cause varies, but includes hydrocephalus, infarcts, tuberculoma formation and hyponatraemia. If the symptoms are thought to be caused by tuberculomas, doctors may re-start or increase the dose of corticosteroids. In this trial, any re-start or dose increase of corticosteroids during the 12-month follow-up will be defined as ’rescue’ corticosteroids.

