### Use of concomitant medication

All other concomitant medications essential for participant management are permitted at enrolment, subject to the exclusion criteria of no contraindications to the use of dexamethasone in the judgement of the attending clinician. If use of a concomitant medication that cannot safely be used with dexamethasone becomes essential after randomisation, then the study drug should be stopped and the concomitant medication used without unblinding. Drugs which increase the risk of gastrointestinal bleeding, such as non-steroidal anti-inflammatory drugs (NSAIDS), should be used with caution. Any other oral or intravenously administered corticosteroids are not permitted, unless deemed essential, in which case the study drug should be stopped and replaced by the chosen corticosteroid. Normal standards of clinical care should be followed.

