### Management of neurological complications occurring after the start of anti-tuberculosis treatment

Corticosteroid use is not routine for the treatment of hydrocephalus or stroke, however for neurological deterioration secondary to tuberculomas most physicians recommend using corticosteroids. In this situation open-label dexamethasone is recommended. High-dose intravenous dexamethasone (0.4mg/kg/24hrs) should be prescribed, and the study drug stopped (if the study drug course is still ongoing).

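### Hepatitis B rule 4 withholds tenofovir by randomised arm, with no exception for placebo participants who later start rescue or replacement corticosteroid

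*Protocol article*

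**What the plan says.** All from the protocol article.

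*Management of hepatitis B* opens with the reason for its rules: "Treating participants infected with hepatitis B (HBsAg positive) with corticosteroids carries a very small risk of reactivation and flare". The items that matter here are:

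- Item 2: all randomised HBsAg-positive participants are unblinded to study drug.
- Item 3: "HBsAg positive participants randomised to dexamethasone (CT- or CC- genotypes) will receive tenofovir therapy at 300mg once daily", for the dexamethasone course and a further 12 months.
- Item 4: "HBsAg positive participants (of any LTA4H genotype) randomised to placebo will NOT receive tenofovir therapy".
- Item 5: HBsAg-positive TT participants, "all of whom will receive open label dexamethasone, will also receive tenofovir therapy at 300mg once daily, according to the current standard of care".
- Item 6: "LFTs and hepatitis B viral load testing will be performed in those participants with hepatitis B who are receiving dexamethasone".

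Two other sections allow corticosteroid after randomisation in either arm. For deterioration due to tuberculomas, *Management of neurological complications occurring after the start of anti-tuberculosis treatment* recommends open-label treatment: "High-dose intravenous dexamethasone (0.4mg/kg/24hrs) should be prescribed, and the study drug stopped". *Use of concomitant medication* bars other systemic corticosteroids "unless deemed essential, in which case the study drug should be stopped and replaced by the chosen corticosteroid".

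*Secondary endpoints – main trial* (d) makes rescue an endpoint ("any re-start or dose increase of corticosteroids during the 12-month follow-up will be defined as" rescue), and *Secondary endpoint analysis* compares it between arms.

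**The concern.** The stated hazard is exposure to corticosteroid, but items 3 and 4 assign tenofovir by randomised arm. In the dexamethasone arm the two coincide, so item 3 causes no difficulty. In the placebo arm they coincide only until a participant starts rescue or replacement corticosteroid. From then on, item 4 as printed keeps prophylaxis away from someone with the very exposure that earns it under items 3 and 5.

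At stake is the safety of a small number of participants and a clear instruction to sites. A clinician who reads item 4 as binding would withhold tenofovir. One who gives it might have to report a deviation, since *Protocol violations* requires all deviations to be reported. Nothing here bears on the validity of the primary comparison.

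**Working it through.** There is no figure in the plan to reproduce. The check is textual, with simple arithmetic on durations and size.

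**Exposure against prophylaxis, HBsAg-positive participants**

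| Group | Corticosteroid after randomisation | Tenofovir as printed |
|---|---|---|
| CC/CT, dexamethasone arm | Study dexamethasone | Yes (item 3) |
| CC/CT, dexamethasone arm, later rescue | Open-label dexamethasone | Yes, item 3 course still running |
| TT | Open-label dexamethasone | Yes (item 5) |
| CC/CT, placebo arm, no rescue | None | No (item 4), consistent with the hazard |
| CC/CT, placebo arm, rescue or replacement | Open-label dexamethasone or other corticosteroid | No (item 4), inconsistent with the hazard |

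Only the last row departs from the stated rationale. The rescue dose of 0.4 mg/kg/24 h IV equals the highest dose in Table 2 (week 1, MRC grades II and III), so this is not a lesser exposure.

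**Cover in the dexamethasone arm.** The course is 6–8 weeks (42–56 days), followed by 12 months (365 days) of tenofovir:

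- 42 + 365 = 407 days from randomisation
- 56 + 365 = 421 days from randomisation

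Both exceed 365 days, so tenofovir is still running at the start of any rescue during follow-up. A study-drug course cut short to a single day would still give more than 365. In the placebo arm, item 4 gives 0 days.

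**Number affected.** With 640 randomised 1:1, the placebo arm has 640 / 2 = 320 participants. The number affected is 320 × HBsAg prevalence × rescue or replacement rate. The article gives neither rate, so the following are assumptions only:

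- Low: 320 × 0.05 × 0.05 = 0.8
- High: 320 × 0.15 × 0.20 = 9.6

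With an assumed flare risk of 1–10%, expected flares run from 0.8 × 0.01 = 0.008 to 9.6 × 0.10 = 0.96.

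**The case against.** The best defence is that item 4 is only a starting allocation. The list runs in order: test at day 0, unblind after randomisation, then sort the unblinded participants by study drug. The sentence after the prohibition explains why unblinding is needed, and says nothing of later open-label treatment. The section on concomitant medication ends by asking for normal standards of care, and item 5 identifies tenofovir with dexamethasone as the Ministry of Health standard for HBsAg-positive patients. Together these make withholding tenofovir the less natural clinical choice. The treating team also knows both HBsAg status and arm. Item 6 monitoring follows dexamethasone exposure whatever the arm, and ALT and bilirubin are measured in everyone. The article is also a condensed account of the full protocol, the risk is described as very small, and every figure for size is assumed.

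Much of this stands as mitigation. The starting-allocation reading may well be what was intended, and the numbers are small and uncertain. But that reading is an inference: item 4 carries no time limit or exception, and neither section that permits corticosteroid refers back to hepatitis B. If normal care means tenofovir while item 4 says it will not be given, two instructions conflict and nothing says which prevails. Monitoring detects a flare but does not prevent one, and item 6 names only dexamethasone, not another replacement corticosteroid. Condensation does not answer the point, because the difficulty is an explicit prohibition in print rather than an omitted detail.

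**Conclusion.** The concern holds, as a minor patient-safety defect in wording. As printed, item 4 leaves HBsAg-positive placebo participants as the one group that can receive corticosteroid after randomisation without tenofovir, contrary to the section's own rationale and to items 3 and 5.

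The size cannot be established from the article. About 1–10 of 320 participants, and fewer than one expected flare, rest wholly on assumed values for HBsAg prevalence, rescue or replacement rate, and flare risk. The upper end combines the highest value of all three. No bias and no effect on sample size, error rates or the primary analysis is claimed.

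**What to change.** Amend item 4 so that HBsAg-positive participants randomised to placebo do not receive tenofovir unless, after randomisation, they start a course of open-label dexamethasone or a replacement systemic corticosteroid. They then receive 300 mg once daily for that course and 12 months beyond it, as in items 3 and 5, with item 6 monitoring applied whichever corticosteroid is used. State that corticosteroid given before randomisation, which the eligibility criteria allow, does not trigger the rule. The sponsor's clinical advisers should set any minimum course length, so that a very short course does not lead to more than a year of tenofovir. Add cross-references to item 4 in the sections on concomitant medication and on neurological complications.

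The change costs one amended item, two cross-references and a note to sites. Item 2 already unblinds these participants, so blinding is unaffected.

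The real cost is supply and handover after month 12. Items 3 and 5 already run 42–56 days past it. The article gives no length for a rescue course; if it is assumed to last 8 weeks (56 days):

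- Rescue starting on day 60: 60 + 56 + 365 = 481, which is 116 days past day 365.
- Rescue starting on day 365 (the latest case): 365 + 56 + 365 = 786, which is 421 days past day 365.

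The amendment should say who provides tenofovir and monitoring over that period.
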